# A multicentre, pragmatic, parallel group, randomised controlled trial to compare the clinical and cost-effectiveness of three physiotherapy-led exercise interventions for knee osteoarthritis in older adults: the BEEP trial protocol (ISRCTN: 93634563)

**DOI:** 10.1186/1471-2474-15-254

**Published:** 2014-07-27

**Keywords:** Knee osteoarthritis, Knee pain, Physiotherapy, Exercise, Primary care, Adherence, Randomised controlled trial

## Abstract

**Background:**

Exercise is consistently recommended for older adults with knee pain related to osteoarthritis. However, the effects from exercise are typically small and short-term, likely linked to insufficient individualisation of the exercise programme and limited attention to supporting exercise adherence over time. The BEEP randomised trial aims to improve patients’ short and long-term outcomes from exercise. It will test the overall effectiveness and cost-effectiveness of two physiotherapy-led exercise interventions (Individually Tailored Exercise and Targeted Exercise Adherence) to improve the individual tailoring of, and adherence to exercise, compared with usual physiotherapy care.

**Methods/design:**

Based on the learning from a pilot study (ISRCTN 23294263), the BEEP trial is a multi-centre, pragmatic, parallel group, individually randomised controlled trial, with embedded longitudinal qualitative interviews. 500 adults in primary care, aged 45 years and over with knee pain will be randomised to 1 of 3 treatment groups delivered by fully trained physiotherapists in up to 6 NHS services. These are: Usual Physiotherapy Care (control group consisting of up to 4 treatment sessions of advice and exercise), Individually Tailored Exercise (an individualised, supervised and progressed lower-limb exercise programme) or Targeted Exercise Adherence (supporting patients to adhere to exercise and to engage in general physical activity over the longer-term). The primary outcomes are pain and function as measured by the Western Ontario and McMaster Osteoarthritis index. A comprehensive range of secondary outcomes are also included. Outcomes are measured at 3, 6 (primary outcome time-point), 9, 18 and 36 months. Data on adverse events will also be collected. Semi-structured, qualitative interviews with a subsample of 30 participants (10 from each treatment group) will be undertaken at two time-points (end of treatment and 12 to 18 months later) and analysed thematically.

**Discussion:**

This trial will contribute to the evidence base for management of older adults with knee pain attributable to osteoarthritis in primary care. The findings will have important implications for healthcare commissioners, general practitioners and physiotherapy service providers and it will inform future education of healthcare practitioners. It may also serve to delay or prevent some individuals from becoming surgical candidates.

**Trial registration:**

ISRCTN: ISRCTN93634563.

## Background

Knee pain in older adults is a common disabling problem, managed in the UK mostly in primary care
[1]. Osteoarthritis (OA) is the most likely underlying diagnosis and refers to a clinical syndrome of joint pain accompanied by varying degrees of function limitation and reduced quality of life
[2]. The most commonly affected peripheral joints are the knees and OA has been shown by radiography to be present in 70% of community dwelling adults aged 50 or more with knee pain
[3]. Structural changes before radiography are common in the remainder
[4]. Clinical trials and systematic reviews consistently show the benefit of exercise, in a variety of forms, for this patient group
[5-9]. Exercise improves muscle dysfunction and reduces pain and disability without exacerbating joint damage
[10]. It can reduce the risk of other chronic conditions
[11] and improve the physical status of people with OA
[12,13]. Physiotherapists are the largest group of exercise advisors for musculoskeletal problems in the UK National Health Service (NHS) and are therefore an appropriate group with which to develop and test strategies to improve outcomes from exercise with older adults with knee pain. Previous studies have shown that older adults with knee pain and physiotherapists involved in their treatment have concerns about the safety of exercise, do not consider exercise as an effective treatment for pain, do not focus on issues of exercise adherence and fail to translate traditional lower limb focused exercise into sustainable lifestyle changes
[14].

The TOPIK trial
[15] tested two primary care services for knee pain in older adults, an enhanced pharmacy review and community physiotherapy (based on advice and exercise) and compared these with advice and self-care alone. At 3 months, pain reduction was three times greater and functional improvement four times greater in those patients randomised to physiotherapy compared with advice alone, and more people obtained clinically meaningful changes
[16,17] than those in the other two groups. Patients received, on average, four physiotherapy treatment sessions. There was evidence that the benefits in pain and function declined in the longer-term, suggesting that most patients require some form of monitoring or regular access to physiotherapy or exercise supervision for potential on-going benefit. The APEX trial
[18,19], which incorporated a more intensive exercise intervention that was supervised and progressed over six treatment sessions, resulted in greater improvements in pain than the exercise programme in the TOPIK trial
[15].

Similarly, other recent trials
[20,21] and reviews
[22] showed small to moderate, short-term reductions in knee pain and disability that are not sustained in the long-term. Exercise is clearly worth doing but we need to find out if, and how, the beneficial effects can be enhanced and maintained, crucial factors in the management of a chronic condition like knee osteoarthritis. Conversations with patients during telephone follow-ups in the APEX trial helped to explain why the effects of exercise might be sub-optimal
[19]. Participants reported misconceptions about exercise in the presence of knee joint damage and pain, difficulty fitting the exercises into a daily routine, overly-complex exercise programmes, insufficient tailoring of the exercise programmes for their individual needs and, in some cases, they simply forgot to do the exercises.

Reviews highlight a lack of information about how to optimise exercise for this patient group
[6-8]. Most studies are short-term, use limited measures of adherence and standardised exercise programmes
[23]. Adherence, independent of exercise type, may be an important factor in the success of exercise interventions. There is evidence that better adherence to exercise improves pain relief
[21] and disability
[23] and that the addition of booster sessions may be helpful in maintaining positive effects on pain and function
[22]. A UK consensus
[24] identified adherence and tailoring of exercise to individuals as important research topics. In the general physical activity literature, a Cochrane review concluded that physical activity programmes that include patient goal setting, individually tailored and written exercise programmes, some professional guidance and ongoing support, may be the most effective approach
[25]. In preparation for the BEEP trial, we conducted two studies. First, a Cochrane systematic review summarising the evidence to date about interventions to improve adherence with exercise in patients with chronic musculoskeletal pain
[26]. Second, the Keele Attitudes and Beliefs Concerning Knee Pain (ABC knee) study investigated the exercise attitudes and behaviours of older adults with knee pain in the community (n = 611) and physiotherapists involved in managing older adults with knee pain (n = 538), to identify potential barriers to, and facilitators of, exercise for knee pain
[14,27-29]. The findings of our Cochrane review, based on 42 trials with over 8,000 patients, suggested using a multifaceted programme combining educational and behavioural strategies to enhance exercise adherence, and incorporating individualisation of the exercise, follow-up and supervision to improve exercise adherence
[26]. No one theoretical model underpinning exercise adherence was shown to be superior and the interventions that incorporated motivational strategies showed promise. A subsequent review by Bennell and Hinman
[30] stated that the optimal exercise dosage is yet to be determined and an individualised approach to exercise prescription is required based on an assessment of impairments, patient preference, co-morbidities and accessibility. They suggested that maximising adherence is a key element dictating success of exercise therapy and that adherence can be enhanced by the use of supervised exercise sessions in the initial exercise period followed by home exercises. Bringing patients back for intermittent consultations with the exercise practitioner, or attendance at ‘refresher’ sessions was also suggested to assist long-term adherence and result in improved patient outcomes. Our ABC knee study showed that whilst physiotherapists use advice and exercise routinely for older adults with knee pain, they do not consider exercise to be an effective treatment for pain, have worries about its safety, provide care over relatively few treatment sessions thus reducing the capacity to adequately individualise, supervise and progress the exercise programme, and do not routinely follow-up patients to check adherence or to support the translation of lower-limb focused exercise into sustainable lifestyle changes in physical activity. Although patients are aware of risk factors (e.g. sedentary lifestyles), they find it hard to make and maintain appropriate lifestyle changes and express the desire for more support from health professionals
[14,27-29]. Marks
[31] describes the many factors that influence exercise adherence in patients with knee OA as either intrinsic (personal factors like self-efficacy, motivation, age, gender, disease status) or extrinsic (e.g. environmental, social factors or other lifestyle issues). These barriers can vary both over time and between individuals, meaning that one single approach to enhancing exercise adherence might not be as effective as an individually tailored approach. The World Health Organisation advocates an “adherence counseling toolkit” that can be used to systematically assess barriers and facilitators to adherence, and suggests that new interventions to enhance adherence are required
[32].

Recent national and international clinical guidelines
[2,24,33] support the overall effectiveness of exercise in knee OA, placing it as a key component of core treatment in primary care. However, there is a lack of evidence around the practical aspects of exercise delivery and maintenance, including how to support individuals to continue to exercise in the longer-term. UK guidelines from the National Institute of Health and Clinical Excellence (NICE) published in 2008 recommended future research should test ways to improve adherence with exercise
[34] and the Chartered Society of Physiotherapy ranked testing ways to help patients incorporate exercise behaviours in their everyday life and increase the long-term effects of exercise as the top musculoskeletal research priority in its national priority setting exercise in 2010
[35].

The Benefits of Effective Exercise for knee Pain (BEEP) trial is a logical consequence of recent primary care trials, systematic reviews and guidelines for knee pain in older adults, which consistently support exercise-based interventions, but highlight the short-term, small to moderate-sized benefits
[2,6]. The overall aim of the BEEP trial is to test, in older adults with knee pain attributable to OA, whether pain and function outcomes can be improved through changing the characteristics of the exercise programme in comparison to usual physiotherapy care. The research hypotheses are i) a physiotherapy-led individualised, supervised and progressed lower limb exercise programme is superior to usual physiotherapy care and ii) a physiotherapy-led intervention targeting exercise adherence in the longer-term and supporting the transition from lower limb exercise to general lifestyle physical activity is superior to usual physiotherapy care. Secondary objectives are to compare the cost-effectiveness of the two exercise interventions compared to usual care and investigate differences in knee pain-related perceptions and expectations, as well as exercise adherence and physical activity. A linked qualitative study exploring participants’ views of the interventions to inform interpretation of the trial results will also be conducted.

## Methods/design

### Design

This is a multi-centre, pragmatic, three-parallel group, assessor-blind, superiority, individually randomised controlled trial comparing two physiotherapy-led exercise-based interventions versus usual physiotherapy care, with embedded qualitative interviews with a subsample of participants. In preparation for this trial, we conducted a small pilot study in two NHS Primary Care Trusts (PCTs) to investigate the feasibility of training physiotherapists in the new treatment approaches, the acceptability of the treatments to patients and physiotherapists and to test the processes for the main trial.

For the main trial, participants are randomised (independently) at each treatment site with block randomisation at a 1:1:1 ratio to usual physiotherapy care (UC), individually tailored exercise (ITE) and targeted exercise adherence (TEA). 500 participants will be recruited over a period of 18 months. Each participant’s involvement with the trial is for 36 months, during which time they will all have access to usual primary care. The primary outcome is assessed 6 months from randomisation, but no analyses will be undertaken until the 18 month follow-up time-point.

### Setting

Participants are recruited from up to 100 general practices and their local physiotherapy services in the West Midlands and North West regions of the UK. Treatments are delivered within physiotherapy centres in up to 6 NHS Primary Care Trusts (PCTs) within the geographical regions of the Primary Care Research Network (PCRN) of the West Midlands North and the North West. The practices and treatment centres include a mix of urban/suburban/semi-rural/rural settings.

### Participants

Participants are eligible for inclusion if they are 45 years old and over, have current knee pain and/or stiffness in one or both knees, are able to read and write in English, are willing to participate, are able to give full informed written consent and have access to a telephone (for minimum data collection). We are deliberately choosing not to restrict the BEEP trial to people with radiographically diagnosed knee OA in order to reflect current clinical practice and national guidance
[2] in which treatment choices are made on the basis of symptoms rather than on radiographic findings. We are thus including people typical of those seen in primary care. Patients recruited through the population survey and the record reviews at participating general practices will have a Chronic Pain Grade
[36] severity of between 2 to 4, determined through a brief postal screening survey. This is to ensure that participants will have a mean level of pain and functional difficulty similar to those patients referred to physiotherapy (determined from our previous trials
[15,19] and that the interventions will be suitable for such patients. Chronic Pain Grade 2 to 4 categories have also been reported as a clinically significant group of knee pain patients in other research studies
[36-38].

Exclusion criteria are as follows: those with potentially serious pathology (such as inflammatory arthritis, malignancy), those who have had a total hip or knee replacement on the affected side, those who are on a waiting list for a total knee or hip replacement, those for whom their knee problem was caused by a recent trauma (sports injury, fall or accident), those for whom exercise interventions are contra-indicated (such as those with unstable cardiovascular disorders, severe hypertension, unstable angina or congestive heart failure), those who have received an exercise programme from a physiotherapist or a knee joint injection in the last three months, those residing in nursing home accommodation, those who are so severely physically restricted that they cannot get to the physiotherapy treatment centres and those who have a close family member already participating in the BEEP trial. Normal recreational involvement in physical activity will not be an exclusion criterion.

### Invitation, recruitment, consent and randomisation

#### Identification of potentially eligible participants

The key learning from the pilot study which recruited participants only from those patients who were already referred by their General Practitioner (GP) to physiotherapy services was the need to increase recruitment to identify all potentially eligible participants. Therefore, in the main BEEP trial participants will be identified in one of three ways: (1) from general practice computer record reviews to identify those who have consulted for knee pain in the last 12 months, (2) from a population survey of older adults registered with participating practices and (3) from patients referred from their general practice to physiotherapy services for knee pain. These will proceed in parallel and are described in more detail below. Duplication checks will ensure that eligible participants are not invited to the BEEP trial more than once. See Figure 
1 for a summary flowchart of the methods to identify and recruit participants.

**Figure 1 F1:**
[figure not shown]
Flow diagram summarising participant recruitment in the BEEP trial.

(1) **General Practice record review:** Members of the Primary Care Research Network (PCRN) informatics team contracted to work in the participating general practices will screen computer records, for adults aged 45 years and over who have consulted with knee pain in the last 12 months at the practice. The electronic screen will identify patients based on the 14 most frequent knee pain related Read codes that have been informed by our previous research
[39]. Read codes are the standard clinical terminology system that GPs enter onto their computer systems in the UK, identifying patients’ clinical symptoms and diagnosis. In addition, the electronic screening protocol will exclude those with potentially serious pathology (e.g. inflammatory arthritis such as rheumatoid arthritis, malignancy etc) and those in nursing home accommodation. GP’s will be invited to screen the sample list and exclude those patients whom they consider inappropriate to be invited to participate in the trial. PCRN staff will then administer the mailing of a short screening questionnaire to check eligibility and determine the patient’s Chronic Pain Grade classification
[36]. Patients recruited through this method must have a Chronic Pain Grade severity of between 2 to 4. The final section of the brief screening questionnaire will ask patients whether they would be happy to give their consent for further contact. Patients will return their screening questionnaires to the Arthritis Research UK Primary Care Centre and only those who are eligible and consent to further contact will form the sample that is sent information about the BEEP trial.

(2) **Population survey:** Older adults (aged 45 years and over) registered with participating general practices will be mailed with a short screening questionnaire to identify potentially eligible trial participants. GP’s will be invited to screen the mailing list and exclude those patients whom they consider inappropriate to be invited to participate in the trial. This screen will be used to identify those in the community with knee pain of sufficient severity
[36] to be included in the BEEP trial, and to exclude those who do not meet the eligibility criteria. Patients recruited through this method must have a Chronic Pain Grade severity of between 2 to 4. The final section of the brief screening questionnaire will ask older adults registered with the practice whether they would be happy to give their consent for further contact. Those who are eligible and consent to further contact will form the sample that is sent information about the BEEP trial.

(3) **Physiotherapy service referrals:** Older adults with knee pain referred by their GP or who self refer to participating physiotherapy services will be first screened, by a member of the physiotherapy service team, for key eligibility criteria (aged 45 years and over, with knee pain and/or stiffness). Those that are potentially eligible will be contacted by a PCRN research nurse to find out if they are willing to receive further information about the BEEP trial.

The three recruitment methods will proceed in parallel until the sample size required is reached, although methods 1 and 2 will be operationalised in different GP practices.

#### Recruitment and consent of participants to the BEEP trial

From identification methods (1), (2) and (3) above, those who meet the eligibility criteria and who agree to further contact will be posted information about the BEEP trial (a cover letter, a participant information sheet (PIS) (See Additional file
1 for a copy of the PIS), a baseline questionnaire, a consent form and a freepost return envelope). No less than 48 hours after receiving the posted information, a PCRN nurse will telephone the person to further check and confirm eligibility. This check will cover the full eligibility criteria in order to ensure that only those who meet these criteria are then recruited to the trial. In addition, the nurse will screen out individuals with known unstable cardiovascular disorders and those who have such severely restricted mobility that they would not be able to get to the physiotherapy clinics for treatment. All potentially eligible participants will have the opportunity to discuss the trial with the research nurse prior to deciding whether or not to participate. Those who wish to take part in the trial will be asked to sign and date the written consent form, supported by the research nurse over the telephone, and return it along with their completed baseline questionnaire to the nurse in a pre-paid envelope. Those who do not wish to take part will be asked to indicate this on the consent form and to return it to the nurse in the pre-paid envelope provided. This consent process was tested in the pilot study and regular audits of the nurse telephone calls will form part of the quality assurance procedures of the BEEP trial. It is possible, based on this consent method, that a very small number of participants in the BEEP trial will be found to be subsequently ineligible since it is only after consent that participants have a detailed physical assessment by a BEEP trial physiotherapist. Examples of this are expected to include a very small number of participants who have radiating leg pain from a spinal problem or a hip joint problem with referred pain in the area of the knee.

Participating general practices will be supported to assist with identification of potentially eligible participants for the BEEP trial through small practice payments to reimburse their time for screening patient lists and physiotherapy services will be supported to participate through financial reimbursement for the time taken out from service delivery for the training programme and additional time for BEEP treatments. Participants will not receive any financial incentives to return screening questionnaires, to take part in the trial or to return their follow-up questionnaires.

#### Randomisation and allocation concealment

Following receipt of a signed consent form and baseline questionnaire, the BEEP trial administrator will randomise the participant using a computer-generated randomisation schedule provided by the Musculoskeletal Clinical Trials Unit (CTU) at Keele University, password-protected to ensure that research nurses and trial statisticians remain blind to treatment allocation. Participants will be individually randomised to one of the three treatment groups using random permuted blocks of size 3. To ensure that patients at each physiotherapy clinic have a chance of receiving any of the interventions, randomisation will be stratified by physiotherapy clinic. Following randomisation, the trial co-ordinator will liaise with the appropriate physiotherapy clinic to arrange the first appointment for each trial participant. The patient will then be informed in writing of the date, time and location of their first appointment in the physiotherapy clinic. The GP of each trial participant will be sent a letter to confirm that their patient is taking part in the BEEP trial. Thus our procedures ensure baseline data are collected prior to randomisation, that the allocation is concealed until after the patient has been recruited into the trial and until the moment of randomisation and that the person assigning participants to intervention groups (study administrator) has no involvement in the eligibility screen, consent or treatment processes.

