### Sources of bias

Selection bias at recruitment will be avoided by separating the processes of determining patient eligibility and treatment allocation and by using random permuted blocks overseen by the CTU, not allowing physiotherapists assessing and treating patients to predict the next allocation in their clinic. Trial participants will know they are having physiotherapy-led exercise and brief details about the three interventions (see Additional file
1 PIS). It is not possible to blind physiotherapists but they will deliver treatment to participants in only one of the three intervention groups. A PCRN nurse blind to treatment allocation will obtain informed consent and oversee the collection of baseline and follow-up questionnaire data, and will collect minimum data over the telephone where necessary. An evaluation of the success of nurse blinding procedures will be completed and a procedure for reporting incidents where blinding has been compromised will be in place.

Data entry, coding, security, storage and management will follow the standard operating procedures in the CTU at Keele University. Data enterers will receive training in line with CTU procedures and will be blind to the identification of the three intervention groups. Random 10% data entry accuracy checks will be conducted at regular intervals, data accuracy will be audited and accuracy rates recorded. The trial statistician (EN) will remain blind until after the creation of a locked analysis dataset at 18 months follow-up and the completion of the primary and secondary analyses.

Comparing available variables between consenting and non-consenting individuals, trial participant withdrawals and completers will be carried out to evaluate external validity. All participants will be free to withdraw from the trial at any time without having to give any explanation. Where possible, we will collect information about the reasons for withdrawal from the trial. Using validated outcome measures will reduce measurement error. Treatment will be recorded by physiotherapists in standardised formats and audits of these case report forms will be undertaken throughout. Feedback to physiotherapists delivering the interventions will be provided, where necessary, so they can modify and improve the delivery of the interventions. Each intervention is supported by a specific protocol and documentation, developed for the BEEP trial and previously tested in the pilot study.

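### Fixed blocks of 3 within clinic let the third allocation in each block be inferred, so the protocol's statement that the blocks prevent prediction is wrong as written

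*Protocol article*

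**What the plan says.** The Design section of the protocol article sets three arms at 1:1:1, randomised independently at each treatment site. Randomisation and allocation concealment adds: "Participants will be individually randomised to one of the three treatment groups using random permuted blocks of size 3", and says that "randomisation will be stratified by physiotherapy clinic". No varying block size is mentioned, and the article does not say that the size is kept from clinics.

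Sources of bias names two protections against selection bias at recruitment. One is the separation of eligibility from allocation. The other is the use of random permuted blocks overseen by the trials unit, described as "not allowing physiotherapists assessing and treating patients to predict the next allocation in their clinic".

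On what reaches the clinic, the same section says: "It is not possible to blind physiotherapists but they will deliver treatment to participants in only one of the three intervention groups". The randomisation section says: "Following randomisation, the trial co-ordinator will liaise with the appropriate physiotherapy clinic to arrange the first appointment for each trial participant".

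On who handles patients before entry, there are three recruitment routes. In route 3, people referred or self-referring to a participating physiotherapy service "will be first screened, by a member of the physiotherapy service team, for key eligibility criteria".

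**The concern.** At 1:1:1 with three arms, a block of 3 is the shortest block possible and the easiest to read. The protocol cites it as a reason why allocations cannot be foreseen, yet it has the opposite property. Physiotherapists are unblinded, each delivers one arm, and the clinic is contacted to book every participant, so a clinic can build up at least part of its own allocation history.

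If someone with influence over entry can foresee the next arm, that knowledge may affect who comes forward. Adjusting for covariates cannot be relied on to remove such an effect. Table 1 shows arms that differ widely in commitment, from up to 4 sessions within 12 weeks to 8 to 10 sessions over 6 months, so staff could have views on who suits which arm. Readers will also take the stated assurance at face value when judging allocation concealment.

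**Working it through.** **Inputs.** Three arms at 1:1:1 (Design). Fixed block size of 3, stratified by clinic (Randomisation and allocation concealment). Planned total of 500 (Sample size).

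**The plan's own figure.** The article gives no figure for predictability. Its computed figure, 129 per group, reproduces: 2 × (1.960 + 0.842)² / 0.35² = 128.1, rounded up to 129, or 387 in total. Block size does not enter it, so the sample size is unaffected.

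**Step 1: predictability as planned.** Assume an observer who knows the block size and all earlier allocations in the clinic in order, and who always names the most likely arm.

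- First place in a block: three arms remain, probability correct 1/3.
- Second place: two arms remain, probability 1/2.
- Third place: one arm remains, probability 1.

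Mean correct guesses = (1/3 + 1/2 + 1)/3 = 11/18 = 61.1%. Share known with certainty = 1/3 = 33.3%. With 500 randomised and all blocks complete, 500/3 gives about 166 certain allocations. Incomplete last blocks in each clinic would lower that a little. Under simple randomisation the figures are 33.3% correct and none certain.

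**Step 2: alternatives.** The fixed sizes were enumerated exactly. The mixtures were simulated over 40,000 allocations with the sizes equally likely. The guesser in the mixtures knows the set of sizes but not the size of the current block.

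| Block scheme | Certain | Guessed correctly |
|---|---|---|
| Fixed 3 (as planned) | 33.3% | 61.1% |
| Fixed 6 | 20.0% | 56.1% |
| Fixed 9 | 14.3% | 53.2% |
| Random 3, 6 | 8.7% | 57.8% |
| Random 3, 6, 9 | 3.8% | 55.5% |
| Random 6, 9 | 5.3% | 54.1% |

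The main gain from varying the size is the loss of certainty (33.3% to 3.8%). Correct guessing falls by only about 6 percentage points and stays well above 33%, as it must in any scheme that keeps the arms closely balanced.

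**Step 3: what one therapist can see.** Each physiotherapist treats in one arm, so none sees the whole sequence directly. A therapist who knows the block size and has just received a patient can infer that nobody else in that block will come to the same arm, but not which of the other two arms is next. The figures in Step 1 need the order of arrivals pooled across therapists.

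**The case against.** The best counter-argument is that knowing the next allocation is not the same as knowing a given patient's allocation. In route 3 the service team applies only basic criteria (age, and knee pain or stiffness). A research nurse then makes contact, information is posted, the nurse telephones at least 48 hours after it arrives to check full eligibility, and consent and the baseline questionnaire come back by post before anyone is randomised. The three routes run in parallel, so other patients may fill the intervening places. Routes 1 and 2 give clinic staff no stated role before randomisation. The nurse is blind to allocation, and the administrator who randomises has no part in screening, consent or treatment. All of this stands, and it limits the harm.

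A reader might infer three stronger things, none of which the article supports:

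- **That every third allocation is certain to the clinic.** This needs the block size, the randomisation order and pooling across single-arm therapists. The article says the clinic is contacted about appointments, not that it learns the order.
- **That staff can steer referrals by arm, so selection bias follows.** Route 3 gives a possible opening, but the postal delay makes timing difficult. The split between routes is not given, and the screening team belongs to the service, which need not be the clinic that forms the stratum.
- **That there is no working safeguard.** Only the block safeguard fails. The separation of eligibility and consent from allocation remains, with a gap in route 3.

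The late discovery of ineligibility, possible because "it is only after consent that participants have a detailed physical assessment by a BEEP trial physiotherapist", is a separate matter. It arises once the allocation exists and does not depend on block length.

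None of this rescues the statement itself, which attributes unpredictability to the blocks. Password protection of the schedule does not help here, since the inference comes from past allocations and not from seeing the list.

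**Conclusion.** The point holds as a contradiction within the protocol and a weak design choice. Fixed blocks of 3 for three arms within clinic make one allocation in three certain and 61% guessable, and Sources of bias says that these blocks do not allow such prediction. The two sections cannot both stand.

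The size is an upper bound: it assumes an observer with the block size and the full ordered history of the clinic. A single therapist has less. The risk that prediction changes who is enrolled is limited by blinded consent, separate randomisation and the postal pathway, and is confined before entry to route 3. The arithmetic is secure. Whether any selection took place cannot be judged from the article.

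**What to change.** Have the trials unit generate the schedule, or its remaining part, with randomly varying block sizes within clinic, for example 3, 6 and 9. Keep the 1:1:1 ratio and the clinic stratification, and do not disclose the sizes to clinics. Since the size of 3 is already in print, the change protects only allocations still to be made. The article does not show how many remained.

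In either case, reword Sources of bias so that protection from selection bias rests on the separation of eligibility and consent from allocation, note the exception for route 3 screening, and drop the claim that blocks of 3 are unpredictable.

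The cost is one regenerated list and some loss of running balance. A block of 9 holds each arm three times, so one arm can lead another within a clinic by at most about 3, against at most 1 now. This is temporary, apart from any unfinished last block, and small beside roughly 500/3 = 167 participants per arm.
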